### Plans to promote participant retention and complete follow-up {18b}

To promote participant retention, this study will provide detailed research information to guardians, including the study background, objective, intervention plan, and participant rights. This ensures that guardians understand the safety and importance of the study and are aware of their right to withdraw or terminate their participation at any time without prejudice. A good communication channel will be established with the guardians to facilitate their interaction with the research team and address any questions or concerns, providing them with reasonable support and assistance.

If the guardians request to no longer receive the originally assigned intervention, the reasons for withdrawal and time point of withdrawal will be fully documented, and researchers will seek consent from the guardians to collect relevant data. If the guardian consents, data collection prior to the withdrawal point will be conducted in accordance with the schedule of recruitment, interventions, and assessments (Fig. 1 in attachment 1). If the guardian refuses, the infants will be withdrawn from the study and replaced.

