### Sample size {14}

As this study aims to compare the effectiveness and safety of NIPPV, CPAP, and HFNC in infants with GA ≥ 32 weeks, we plan to conduct paired comparisons. Since no studies with identical content to this study have been conducted in the past, we will refer to the following studies for sample size calculation. A trial comparing CPAP and BiPAP including neonates of GA ≥ 34 weeks with transient tachypnea of the newborn, showed that BiPAP had lower treatment failure (CPAP: 20%, BiPAP: 7.9%, P: 0.03) [42]. In addition, a prospective randomised controlled trial comparing CPAP and HFNC in infants with GA ≥ 31 weeks showed higher treatment failure in the HFNC group (HFNC: 20.5%, CPAP: 10.2%, CI: 10.3) [34]. Therefore, we can calculate the sample size of this trial based on the data from the study [34], in which we will use the treatment failure of HFNC and CPAP as primary respiratory support in neonates as a reference. Considering the trial involving multiple comparisons, using an alpha error rate of 0.0167 and a power of 0.8, at least 252 infants should be enrolled in each arm calculated by PASS15.0.5 software, so the total sample size is 756. Considering 5% loss, the sample size would be no less than 795.

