## Statistical methods

### Statistical methods for primary and secondary outcomes {20a}

Statistical analysis will be performed on the basis of intention-to-treat analysis, according to the Consort reporting guidelines. The normality of continuous outcomes will be tested by Kolmogorov–Smirnov test. Mean difference with 95% confidence interval (CI) will be calculated for normally distributed outcomes and median difference with P25-P75 for non-normally distributed continuous outcomes. Continuous outcomes will be compared by the appropriate parametric (one- way ANOVA) or non-parametric (Mann–Whitney U) test, followed by post hoc test if needed. Dichotomous outcomes will be compared by Chi-square test. Multivariate regression analyses will also be conducted for selected outcomes, if required, and in that case, logistic regression, linear regression, or Cox regression analyses will be performed based on the type and distribution of variables. Specifically, if a baseline characteristic of the enrolled population shows a significant difference (*p* < 0.2) between the two groups in the univariate analysis, the results will be adjusted for that variable. To control for the error of multiple comparisons, the *P*-value of multiple comparisons will be corrected by Bonferroni method. All tests will be two-tailed, and *P* < 0.0167 will be considered significant.

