### Methods in analysis to handle protocol non-adherence and any statistical methods to handle missing data {20c}

For infants lost to follow-up, multiple imputation will be used to replace missing values for primary and secondary outcomes. The *P* < 0.0167 will be considered statistically significant.

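### Withdrawing and replacing a randomised infant, and ending data collection when the assigned mode is stopped, conflicts with the stated intention-to-treat analysis and can bias the 72 h comparison

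*Protocol article*

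**What the plan says.** Four sections of the protocol article bear on the same infant.

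- **Retention {18b}.** The trigger is a request about treatment: "If the guardians request to no longer receive the originally assigned intervention". Two branches follow. Where the guardian agrees to data collection, "data collection prior to the withdrawal point will be conducted in accordance with the schedule". Where the guardian does not, "If the guardian refuses, the infants will be withdrawn from the study and replaced".
- **Statistical methods {20a}.** "Statistical analysis will be performed on the basis of intention-to-treat analysis, according to the Consort reporting guidelines".
- **Missing data {20c}.** "For infants lost to follow-up, multiple imputation will be used to replace missing values for primary and secondary outcomes". Infants who have been replaced are not mentioned.
- **Sample size {14}.** The target of 756 is already raised for attrition: "Considering 5% loss, the sample size would be no less than 795".

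Section {11b} lists a guardian's request among the grounds for ending the assigned mode, so the situation is foreseen. The primary outcome in {12} is treatment failure within 72 h of randomisation. Sections {17a} and {17b} describe open-label care in which only outcome assessors and data analysts are blinded.

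**The concern.** Intention-to-treat means that every randomised infant counts in the arm to which it was allocated. An infant who is withdrawn and replaced does not. A substitute recruited later is a different infant with its own randomisation and cannot stand in for the first.

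The agreement branch is milder but still loses information. Collection covers only the time before the mode was stopped. If the infant had not met a failure criterion by then, its 72 h status is unknown and must be imputed, although the infant may still be an inpatient and observable. Imputation would then rest on missingness at random, which is doubtful if guardians ask to stop because the infant is deteriorating.

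The selection is made by people who know the mode. Blinded assessors and analysts cannot correct it, because it happens before outcomes reach them. If it differs by arm and is related to outcome, the primary comparison is biased. The direction depends on which arm loses the infants at higher risk.

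**Working it through.** **Inputs from Sample size {14} and Statistical methods {20a}:** failure 20.5% (HFNC) and 10.2% (CPAP); 252 per arm; two-sided alpha 0.0167, so z = 2.393; power 0.80, so z = 0.842; 5% loss.

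**Reproducing the plan's figure.** With unpooled variance:

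n = (2.393 + 0.842)² × (0.205×0.795 + 0.102×0.898) / 0.103² = 251.1, which rounds up to 252.

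Three arms give 756. Allowing 5% loss gives 756/0.95 = 796 or 756×1.05 = 794; the plan's 795 lies between. The sample size is not in error. Power at 252 per arm is 80.2% unpooled and 79.5% with a pooled test.

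**Inputs not in the documents (assumptions).** w is the share of an arm excluded. f is the failure risk among those excluded. The failure rate in the infants who remain is

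p_obs = (p − w·f) / (1 − w).

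The analysed number is held at 252 per arm, so the results show the effect of exclusion alone.

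**A. True rates 20.5% and 10.2%, exclusion from the HFNC arm only.** Power = Φ(d/SE − 2.393), where d is the observed difference and SE is unpooled. Worked case, w = 0.05 and f = 0.5: p_obs = (0.205 − 0.025)/0.95 = 18.9%; d = 8.7 points; SE = 0.0312; d/SE = 2.80; power = Φ(0.41) = 66%.

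| w | f | Observed HFNC failure | Power |
|---|---|---|---|
| any | 0.205 (unrelated to failure) | 20.5% | 80% |
| 1% | 0.5 | 20.2% | 78% |
| 2% | 0.5 | 19.9% | 75% |
| 5% | 0.3 | 20.0% | 76% |
| 5% | 0.5 | 18.9% | 66% |
| 5% | 0.8 | 17.4% | 48% |
| 10% | 0.5 | 17.2% | 46% |

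The pooled test gives values about one point lower or less.

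**B. Exclusion from both arms, w = 0.05 and f = 0.5 in each.** HFNC becomes 18.9% and CPAP (0.102 − 0.025)/0.95 = 8.1%. The difference is 10.8 points and apparent power rises to 89%. The bias need not run against HFNC v CPAP.

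**C. No true difference, exclusion from one arm, w = 0.05 and f = 0.5, pooled test.**
- Both true rates 10.2%: the affected arm shows 8.1%, a spurious difference of 2.1 points; type I error about 0.058.
- Both true rates 20.5%: the affected arm shows 18.9%, a spurious difference of 1.6 points; type I error about 0.028.

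The nominal level is 0.0167 in both.

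**The case against.** Several stronger readings are tempting, and the text does not support them.

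- **That any request to stop the mode counts as leaving the study.** Only the refusal branch of {18b} uses that language, and {11b} treats stopping the mode as a separate matter. Replacement needs both a request to stop and a refusal of data collection, which may be rare.
- **That the primary outcome is always lost in the agreement branch.** A failure recorded before the request is kept, and under {11b} meeting a failure criterion itself ends the mode. What is lost is the status of infants who had not yet failed. Section {20c} could impute it, and the phrase limiting data to the earlier period may be loose drafting.
- **That the figures measure harm from replacement.** They come from exclusion. Deleting the replacement clause alone would leave them unchanged.
- **That a large loss of power is to be expected.** The larger losses need exclusion that is outcome-related and concentrated in one arm, at 5% or more. At 1% or 2% the effect is small, and with both arms affected apparent power can rise.
- **That the 5% allowance and the imputation contradict replacement.** They make replacement unnecessary for protecting numbers, which is a different point.

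The conflict itself stands. No other section returns a replaced infant to the analysis, and imputation for infants lost to follow-up does not mention one. A later analysis plan could not fully repair this, because {18b} governs what is collected and who remains enrolled.

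**Conclusion.** The concern holds as a conflict between {18b} and the intention-to-treat commitment in {20a}. Replacement of a randomised infant has no reading that fits that commitment. The rule for guardians who agree to data collection is a lesser fault: as written it ends collection early and moves avoidable missing data into imputation.

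The possible bias runs from nil to material, and the documents do not show where in that range the trial would fall. It is nil if exclusion is unrelated to failure. With half of those excluded from HFNC failing, power is about 78% to 75% at 1% to 2% excluded, and 66% to 46% at 5% to 10%. Under equal rates of 10.2%, 5% excluded from one arm on the same terms raises type I error to about 0.058. All of this assumes the planning rates, 252 analysed per arm and, except in case B, exclusion from a single arm. The stated sample size needs no change.

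**What to change.** 1. In {18b}, delete the words on replacement and rely on the 5% allowance already in {14}.
2. Separate stopping the assigned mode from refusing data collection. Where only the mode is stopped and the guardian agrees to data collection, collect all outcomes to 72 h and to discharge, and analyse the infant as randomised.
3. Where data collection is refused, keep the infant in the randomised denominator of the allocated arm with a missing outcome. Use only data that the guardian permits. Analysing everything gathered before the refusal could override it, since consent for that earlier period is what {18b} seeks.
4. Extend the imputation in {20c} to these infants, and add a sensitivity analysis counting them as failures.

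The cost is protocol and consent wording, a little more data collection and one further analysis. Much of the outcome data comes from bedside forms and hospital records already in use ({19}), though the nasal trauma and comfort scores need bedside assessment. No change to the sample size is required.

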### Data management {19}

An electronic medical record form will be generated for each enrolled infant to facilitate data collection and management. Respiratory therapists and doctors involved will fill out bedside record forms, which includes ventilatory parameters, blood gas values (PaO_2_, PaCO_2_, pH), and SpO_2_. Data obtained from the bedside record forms and the hospital medical record system (HIS system) will be entered into the electronic medical record form by the data managers. These personnel will receive relevant training to ensure the accuracy, completeness, and confidentiality of the data. The electronic medical record form will be archived in real-time on the online system, with access restricted to authorized personnel only. The principal investigator will periodically review the data, identify missing or erroneous data, and urge local researchers to complete the necessary information (Fig. 2).

### Confidentiality {27}

Each enrolled patient has an independent number and center number, which can only be identified by combining the two. No researcher may disclose patient identity information outside the hospital.

### Plans for collection, laboratory evaluation and storage of biological specimens for genetic or molecular analysis in this trial/future use {33}

There is no plan to collect any biological material samples in this study.

## Statistical methods

### Statistical methods for primary and secondary outcomes {20a}

Statistical analysis will be performed on the basis of intention-to-treat analysis, according to the Consort reporting guidelines. The normality of continuous outcomes will be tested by Kolmogorov–Smirnov test. Mean difference with 95% confidence interval (CI) will be calculated for normally distributed outcomes and median difference with P25-P75 for non-normally distributed continuous outcomes. Continuous outcomes will be compared by the appropriate parametric (one- way ANOVA) or non-parametric (Mann–Whitney U) test, followed by post hoc test if needed. Dichotomous outcomes will be compared by Chi-square test. Multivariate regression analyses will also be conducted for selected outcomes, if required, and in that case, logistic regression, linear regression, or Cox regression analyses will be performed based on the type and distribution of variables. Specifically, if a baseline characteristic of the enrolled population shows a significant difference (*p* < 0.2) between the two groups in the univariate analysis, the results will be adjusted for that variable. To control for the error of multiple comparisons, the *P*-value of multiple comparisons will be corrected by Bonferroni method. All tests will be two-tailed, and *P* < 0.0167 will be considered significant.

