### Objectives {7}

The objective of this study is to compare the clinical effectiveness of HFNC, CPAP, and NIPPV as primary respiratory support in neonates with RD who are ≥ 32 weeks GA in reducing the need for IMV. We hypothesize that NIPPV is more effective than CPAP and HFNC in preventing treatment failure in neonates ≥ 32 weeks GA.

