#### Secondary outcomes

Death before discharge.Surfactant treatment within 72 h after randomization.Duration of both NIV and IMV.Duration of oxygen therapy.Bronchopulmonary dysplasia (BPD).Time to achieve full enteral nutrition.Necrotizing enterocolitis.Duration of admission.Cost of admission.Air leak syndrome (including pneumothorax, pneumomediastinum, and pneumopericardium).Nasal trauma, which will be assessed based on a clinical score [40].Comfort score (Neonatal Pain, Agitation and Sedation Scale, N-PASS) [41].

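### If infants never ventilated count as 0 h, the planned median difference for duration of invasive ventilation is 0 at IMV rates near the planning failure rates, even when the arms differ

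*Protocol article*

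**What the plan says.** All in the protocol article:

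- **Statistical methods {20a}** sets the analysis basis: "Statistical analysis will be performed on the basis of intention-to-treat analysis". Normality is checked by Kolmogorov–Smirnov. Where it fails, the effect is given as "median difference with P25-P75 for non-normally distributed continuous outcomes" and the test is the "non-parametric (Mann–Whitney U) test, followed by post hoc test if needed". Regression is allowed for selected outcomes if required; IMV duration is not named among them.
- **Secondary outcomes** lists "Duration of both NIV and IMV". It states no population, no rule for infants who are never ventilated, and no time limit. No secondary outcome counts the infants who receive IMV.
- **Exclusion criteria** rule out infants already intubated or judged to need intubation, so IMV time starts at zero for everyone.
- **Sample size {14}** cites failure rates from two trials, "HFNC: 20.5%, CPAP: 10.2%, CI: 10.3" and "CPAP: 20%, BiPAP: 7.9%, P: 0.03", and plans 252 infants per arm.
- **Objectives {7}** compares the three modes "in reducing the need for IMV".

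**The concern.** A median describes a duration only if at least about half the infants have some of it. Here IMV is what the assigned modes are meant to prevent, and the protocol's own rates suggest that most infants will never receive it. One rule for all skewed outcomes then gives this outcome a median of 0 in each arm and a difference of 0, even where one mode halves the use of IMV.

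IMV duration is the only listed secondary outcome that measures IMV, and need for IMV is named in the objective. A reader could meet a significant rank test beside an estimated difference of 0 and be unable to tell how large the effect is.

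**Working it through.** **Inputs.** From the protocol article: n = 252 per arm, two-sided alpha 0.0167, and failure rates of 20.5% and 10.2% (HFNC, CPAP) and of 20% and 7.9% (CPAP, BiPAP). Assumed: the IMV rate equals the failure rate; never-ventilated infants count as 0 h; durations among the ventilated are lognormal with log-SD 0.8. The last assumption matters only for the hours and the power figures, not for the zero median.

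**1. The plan's own figure.** The unpooled normal formula gives
n = (2.393 + 0.842)² × (0.205×0.795 + 0.102×0.898) / 0.103² = 10.464 × 0.25457 / 0.010609 = 251.1, so 252 per arm. The stated size is reproduced, and 20.5% versus 10.2% is its basis.

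**2. Share with zero IMV** (1 − rate): 79.5%, 80.0%, 89.8% and 92.1%.

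**3. Chance that an arm's median exceeds 0.** With 252 infants the median is the mean of the 126th and 127th ordered values, so at least 126 must be ventilated. Binomial tail P(X ≥ 126):

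| Ventilated | P(median > 0) |
|---|---|
| 20.5% | 2.6×10⁻²⁵ |
| 30% | 2.5×10⁻¹¹ |
| 40% | 0.0008 |
| 45% | 0.06 |

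The result survives an IMV rate well above the planning rates and gives way only near 50%.

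**4. Upper quartile.** P75 is clearly above 0 if at least 64 of 252 are ventilated: 3.5% at a rate of 20.5%, 47% at 25%, 95% at 30%. (Quartile definitions that interpolate need only 63, which gives 4.8% at 20.5%.) So P75 is usually 0 at about 20% ventilated, but not at 25–30%.

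**5. Hodges–Lehmann reading of the median difference.** The share of between-arm pairs with both values 0 is 0.795×0.898 = 71.4%, or 0.800×0.921 = 73.7% for the other trial. Both exceed one half, so the median of pairwise differences is also 0.

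**6. What the median misses.** With a median of 72 h among the ventilated in both arms, their mean is 72×exp(0.8²/2) = 99.2 h. The difference per randomised infant is 99.2×(0.205 − 0.102) = 10.2 h. With medians of 48 h or 120 h it is 6.8 h or 17.0 h. In simulation (252 per arm, 400 runs) the median difference and the Hodges–Lehmann estimate were exactly 0 in every run at 20.5% versus 10.2%. They stayed at 0 with medians of 144 h versus 48 h among the ventilated, where the mean difference was about 33 h.

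**7. The planned test.** At 20.5% versus 10.2% with equal durations, Mann–Whitney gave P < 0.0167 in 78% of those runs, and in 79% of 2,000 further runs. Its power comes mainly from the share ventilated: with 20.5% in both arms and medians of 144 h versus 48 h, it rejected in only about 5% of runs.

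**The case against.** **Zero-coding is not written, and an unseen analysis plan may settle it.** True. But the article does state intention to treat and does fix the effect measure, and together these imply zeros. Two other readings avoid them. Summing noninvasive and invasive time is possible but less natural, and it would hide IMV. Restricting to ventilated infants departs from intention to treat, because it compares groups selected by an event that the modes are meant to change.

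**The failure rate is not the IMV rate.** This stands. Failures managed without intubation would lower the IMV rate. IMV after 72 h would raise it, as would intubation for surfactant (INSURE) if counted, which the article does not settle. A reader might take the 72 h failure rate as an upper bound on IMV before discharge; the documents do not support that. The zero median tolerates the uncertainty (step 3). A claim that the quartiles are almost always 0 to 0 does not (step 4).

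**The analysis does register a difference.** A reader might infer that the plan would report nothing whatever the modes do. That goes too far: the rank test keeps about 80% power in the planning scenario, and regression is available if required. What fails is the estimate of size.

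**The main question does not rest on this outcome.** Correct. Treatment failure is binary, includes situations requiring intubation, and is compared by chi-square.

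**Conclusion.** The point holds for the effect estimate of one secondary outcome. With never-ventilated infants at 0 h and IMV rates near 7.9% to 20.5%, the planned median difference is 0 with near certainty, and it stays 0 for any effect that leaves each arm clearly below 50% ventilated. The Mann–Whitney P value remains informative, so the likely result is a P value without a usable effect size. The hours in step 6 rest on assumed durations and are illustrative. The primary outcome and the sample size are unaffected. The change is worth making because IMV is named in the objective and the data will be collected anyway.

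**What to change.** In Statistical methods {20a}, exempt IMV duration from the normality-test and median rule, and state that never-ventilated infants count as 0 h. For each pair of arms report:

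- the difference in the proportion receiving IMV; and
- the difference in mean IMV hours per randomised infant, with a bootstrap interval.

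Both intervals should be at the adjusted level (1 − 0.0167, about 98.3%). Present deaths alongside, because early death shortens IMV hours and would otherwise look like benefit. Show the median among ventilated infants as description only, without a between-arm test. State also whether intubation for surfactant counts as IMV time.

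The cost is a few sentences and a short bootstrap, with no new patients or data. The mean is sensitive to a few long ventilation courses, which widens its interval. Other summaries, such as ventilator-free time, could also serve; what matters is that the choice is fixed before the results are seen.

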Many studies have shown that NIPPV is superior to CPAP in reducing tracheal intubation and apnea in neonates with GA < 32 weeks [21–24]. When compared to CPAP, NIPPV exhibits significant reductions in respiratory failure, apnea, tracheal intubation, and extubation failure among preterm infants born before 37 weeks [25–27]. However, there is a relative scarcity of evidence regarding the comparison between NIPPV and CPAP specifically in neonates with GA ≥ 32 weeks. Further studies in this population are warranted to provide a clearer understanding of the effectiveness of NIPPV in comparison to CPAP.

There is limited evidence comparing the effectiveness of NIPPV and HFNC in neonates with GA ≥ 32 weeks. Two randomized controlled studies [28, 29] have been conducted, one including neonates with GA less than 35 weeks and the other including neonates with GA less than 34 weeks. These studies reported no significant difference between HFNC and NIPPV in preventing treatment failure. However, it is important to note that the sample sizes of these two studies were relatively small, suggesting the need for larger-scale research to further investigate and validate these findings.

Several studies have provided evidence supporting the superior outcomes of NIPPV over CPAP in terms of reduced treatment failure rates and tracheal intubation incidents [21–24]. However, due to the higher cost and greater technical complexity of NIPPV equipment, many clinical centers prefer to use CPAP as the primary respiratory support for neonates [30]. It has been reported that neonates with higher respiratory scores [31] have a higher increase in the need for respiratory support within 24 h [32]. In the case of neonates with GA ≥ 32 weeks, some individuals present with severe RD, and early implementation of more advanced NIV methods may potentially prevent the exacerbation of their condition, consequently reducing the incidence of tracheal intubation and mechanical ventilation. Therefore, our proposed research plan includes a subgroup analysis based on the severity of RD, aiming to investigate the effectiveness of NIPPV, CPAP, and HFNC in preventing treatment failure among neonates with varying degrees of RD severity.

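### Cost of admission will in practice be tested by Mann-Whitney and summarised by a median difference; neither addresses mean cost per infant, so a real saving from prevented failures could largely be missed

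*Protocol article*

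**What the plan says.** All of this is in the protocol article.

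- Secondary outcomes lists "Cost of admission". No analysis specific to cost appears anywhere.
- Statistical methods {20a} applies one gate to everything continuous: "The normality of continuous outcomes will be tested by Kolmogorov–Smirnov test".
- An outcome that fails the gate is summarised by a "median difference with P25-P75 for non-normally distributed continuous outcomes". A mean difference with a 95% confidence interval is kept for outcomes judged normal.
- The test follows the same split: "Continuous outcomes will be compared by the appropriate parametric (one- way ANOVA) or non-parametric (Mann–Whitney U) test".
- Regression is a further possibility: "Multivariate regression analyses will also be conducted for selected outcomes, if required". Cost is not named as one of the selected outcomes.
- Background {6a} mentions cost as a barrier: "due to the higher cost and greater technical complexity of NIPPV equipment, many clinical centers prefer to use CPAP". Objectives {7} states the expected benefit: "We hypothesize that NIPPV is more effective than CPAP and HFNC in preventing treatment failure".

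**The concern.** A unit that asks what a ventilation mode costs wants the cost per infant treated, because that figure times the number of infants is the bill. This is an arithmetic mean. The null of Mann-Whitney is that an infant drawn from one arm is as likely to cost more as to cost less than an infant drawn from the other, which is not equality of mean cost. A median takes no account of how expensive the expensive admissions are.

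The two questions part when a mode adds something to the routine cost of most infants and spares a minority an expensive failure. The saving then sits in the upper tail, which ranks compress and the median ignores. At stake is whether the cost result can show a real saving, and whether the reported difference has the right sign. Using a three-arm rank test, or a proper interval around the median, would not help, because the target would still not be mean cost.

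**Working it through.** **Inputs from the protocol article.** Sample size {14}: 252 per arm, alpha 0.0167, failure rates 20% vs 7.9% (CPAP vs BiPAP) and 20.5% vs 10.2% (HFNC vs CPAP). Statistical methods {20a}: two-sided tests.

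**Check of the inputs.** There is no cost figure to reproduce. The sample size does reproduce. With unpooled variances, n = (2.393 + 0.842)² × (0.205×0.795 + 0.102×0.898) / 0.103² ≈ 251.1, so 252.

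**Assumptions, since the protocol gives no cost data.** Routine cost is lognormal with mean 1 and CV 0.5–0.8. A failure adds 2–4 times routine cost, also lognormal. The mode with fewer failures has its routine mean raised by a proportion u.

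**Mean cost.** With rates 20% vs 7.9% and extra cost E:
- higher-failure arm: 1 + 0.20E
- lower-failure arm: 1 + u + 0.079E
- difference: u − 0.121E

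For E = 3 and u = 0.05 this is 0.05 − 0.363 = −0.313, a true saving. For E = 2 and u = 0.15 it is 0.15 − 0.242 = −0.092, still a saving.

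**Which route applies.** In simulated samples Kolmogorov–Smirnov rejected normality in 99–100%, so cost would go to Mann-Whitney and the median.

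**Small uplift (5–15%), mode truly cheaper.**
- Mann-Whitney calls it significantly dearer in about 0–2% of trials (up to about 3% with 20.5% vs 10.2%).
- At 5% uplift and E = 3, Mann-Whitney detects the saving in about 20% of trials, a comparison of means in 40–71%.
- At 5% the median difference still has the right sign (−0.05 to −0.09) but is far smaller than the mean saving (−0.313 at E = 3). At half the break-even uplift for E = 3 (0.363/2 ≈ 0.18) the true mean difference is −0.18, while the median difference is +0.02 to +0.07.

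**Uplift that makes mean costs equal (u = 0.121E).**

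| Failure adds | Uplift needed | Mann-Whitney rejects, CV 0.5–0.8 | At CV 1.2 |
|---|---|---|---|
| 2 times | 24% | 7–25% | about 4% |
| 3 times | 36% | 26–74% | about 10% |
| 4 times | 48% | 59–97% | about 29% |

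In the CV 0.5–0.8 runs practically all these rejections call the lower-failure mode dearer. Welch stays at about 1–2%. With 20.5% vs 10.2% the uplifts are 0.103E (21%, 31%, 41%) and the rates about 5–17%, 18–57% and 42–89%.

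**A different cost model.** Take base cost 100, a failure costing 4 times as much (so adding 300), a fixed add-on of 15 for every infant, and rates 20.5% vs 10.2%. True means are 100 + 0.205×300 = 161.5 and 115 + 0.102×300 = 145.6, a saving of 15.9. At CV 0.3 the medians are 105.4 and 114.8. Mann-Whitney calls the cheaper mode significantly dearer in 40% of trials, and Welch calls it cheaper in 18%. At CV 0.5 the 40% falls to 10%. With an add-on of 5 it is 0.2% at either CV.

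**The case against.** A reader might infer that the plan will often declare NIPPV significantly dearer when it adds only a little to each infant's cost. The documents do not support that.

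- The high rejection rates in the table need routine uplifts of 24–48%, which are not small.
- Background {6a} speaks of equipment cost and does not say that each admission costs more. Ventilators gives the same example devices for all three modes, and Study setting {9} says the centres already have machines that can deliver each mode.
- The infants range from 32 weeks to term, so costs may vary widely. In the proportional model, wider spread lowers the rejection rates.

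These points stand, and they limit the claim.

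Three more points carry less weight. First, the objectives are clinical and no budget question is stated, so a median could describe a typical admission. That is fair as description. It does not make the median or the rank test an answer to what a mode costs per infant, and the Background itself treats cost as a reason for choosing between modes. Second, methods for cost are often left to an analysis plan, which is not shown. But the article does not stay silent: it states a rule for every continuous outcome and makes no exception for cost. Third, linear regression, which models means, is allowed. It is optional and not tied to cost.

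**Conclusion.** The point holds in limited form. The stated rule sends cost of admission to a test and a summary that do not address mean cost per infant. With routine uplifts of about 5–15% and CV 0.5–0.8, the main harm is a missed saving, together with a median difference that shrinks towards zero or changes sign as the uplift grows. Significant naming of the wrong arm is then rare (about 0–3%) if the uplift is proportional to routine cost. It becomes frequent when the uplift is near break-even, or when a fixed add-on of about 15% meets a tight spread (CV 0.3). Nothing in the protocol establishes either case.

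All sizes rest on assumed costs. A comparison of means keeps its error rate and points the right way, but its power can be modest. Cost is one of 12 secondary outcomes and the primary result is untouched, so this is a desirable improvement, not a serious defect.

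**What to change.** In Statistical methods {20a}, take cost of admission out of the normality rule. State that, for each pair of arms, the difference in arithmetic mean cost per infant will be reported with a bootstrap (for example bias-corrected) or Welch confidence interval, whatever the distribution. Keep the median and quartiles as description.

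This takes one sentence and a short computation on data already being collected, with no extra infants. It should be settled before the data are analysed. The downside is a wider interval when a few admissions are very costly.
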